**A randomised controlled trial of the effect of diatary and/or physical**

**activity intervention in obese pregnant women**

PROJECT GROUP

Departmental Physician [name] 1

Consultant [name] 1

Consultant [name] 1

Professor, [name] 1

Consultant [name] 1

Consultant [name] 2

Clinical Dietician [name] 2

Senior Research, [name] 3

1: Gynaecologic Obstetric Department

2: Endocrinologic Department

Hvidovre Hospital

[name]

[name]

3: Department for Epidemiologic Research

Statens Serum Institut,

[name]

[name]

PROJECT LEADER

[name]

Translation from Danish by:

[name]., DMSci.

[name]

Århus University Hospital,

Denmark.

The following projects are planned.

1. **Randomised intervention study: Effect of physical activity measured by pedometer and intensive dietary intervention in obese pregnant women with BMI≥30 kg/m².**

A randomised intervention study comparing standard dietary advice regimen with a recommendation of increased physical activity monitored by pedometer together with and without intensive dietary advice based on a Mediterranean diet. Intensive dietary advice given by a dietician and checked ever other week alternately by personal appearance or telephone consultation

**PURPOSE:**

- To illustrate the effect of intervention on activity level, diet, weight gain, glucose tolerance, lipid profile in test subjects and clinical parameters in the child.
- To illustrate factors that influence participation and compliance in connection with life-style intervention.

1. **Questionnaire study. Investigate dietary habits/dietary changes in obese pregnant women with BMI≥30 kg/m², with great and low weight gain during pregnancy:**

Detailed dietary history (360 questions) taken at the beginning and end of pregnancy as was used and validation in the study: “Better health for mother and child”

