**Method:**

After the first visit to the dietician during which a detailed dietary history is taken, all included obese pregnant women will be telephone randomised 1:1:1, to intervention groups 1, 2 or to general standard regimen for all obese pregnant women as given above.

**Intervention aim:** Weight gain: <5 kg

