**Intervention group 1:**

- Receive follow-up dietary advice by alternatively personal or telephone contact every 2nd week. Given pedometer and advised to take 11,000 steps/day. This corresponds to 150 % of average for pregnant women, determined in previous project. Activity monitored for 7 consecutive days every 4th week.
- Follows in addition the normal pregnancy program and the other aspects of the standard regimen.

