**Intervention group 2:**

- As intervention group 1, but without intensive follow-up by dietician.

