**Procedure for the 5 groups of pregnant women:**

1. Intervention group 1:
   - After the consultation with the dietician, the project leader assures that the history form is filled out and goes through it with the pregnant women.
   - Project leader informs about dietician follow-up program.
   - Project leader hands out pedometer and encourages a step count of 11,000 steps a day. Together with the pedometer is given: 7 copies of week-form for registration of step count (Appendix 2) and 7 return envelopes so that the week-forms can be returned on-going. Those included measure physical activity during 1 week every 4th week during the whole pregnancy. (circa GA 14,18, 22, 26, 30, 34, 38) On this form current weight is noted. The first pedometer week beginning as soon as possible from GA 14+0. SMS contact from project leader the day before the start of every registration week is offered. Written permission for this is obtained. (Appendix 6)
   - Maternal weight noted.
   - US planned by project leader at GA 37-38.
2. Intervention group 2:
   - After the consultation with the dietician, the project leader assures that the history form is filled out and goes through it with the pregnant women.
   - Project leader informs about dietician follow-up program.
   - Project leader hands out pedometer and encourages a step count of 11,000 steps a day. Together with the pedometer is given: 7 copies of week-form for registration of step count (Appendix 2) and 7 return envelopes so that the week-forms can be returned on-going. Those included measure physical activity during 1 week every 4th week during the whole pregnancy. (circa GA 14,18, 22, 26, 30, 34, 38) On this form current weight is noted. The first pedometer week beginning as soon as possible from GA 14+0. SMS contact from project leader the day before the start of every registration week is offered. Written permission for this is obtained. (Appendix 6)
   - Maternal weight noted.
   - US planned by project leader at GA 37-38.
3. Pregnant women who follow usual pregnancy programme and standard regimen.

- After consultation with dietician, the project leader assures that the history form is filled out and goes through it if necessary with the pregnant women.
- Then pregnant women follow hereafter the usual pregnancy programme and standard pregnancy regimen.
- US planed by project leader at GA 37-38.

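### The stated effect on activity level cannot be estimated from the measurements described: step counts are planned only in the two pedometer groups and only after the step target is given

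*Protocol*

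**What the plan says.** The Purpose section for the randomised study opens with "To illustrate the effect of intervention on activity level, diet, weight gain, glucose tolerance, lipid profile in test subjects". A second bullet deals separately with participation and compliance.

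The project description on the opening page presents the trial as "comparing standard dietary advice regimen with a recommendation of increased physical activity monitored by pedometer together with and without intensive dietary advice". Under Method, "all included obese pregnant women will be telephone randomised 1:1:1, to intervention groups 1, 2 or to general standard regimen".

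Activity measurement is described by group:

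- **Intervention group 1:** "Given pedometer and advised to take 11,000 steps/day". The target is explained by "This corresponds to 150 % of average for pregnant women, determined in previous project".
- **Intervention group 2:** "As intervention group 1, but without intensive follow-up by dietician".
- **Both pedometer groups** (Procedure for the 5 groups): "Project leader hands out pedometer and encourages a step count of 11,000 steps a day". Seven week-forms are supplied, for registration at about GA 14, 18, 22, 26, 30, 34 and 38.
- **Standard regimen** (same section): the history form is checked, and "Then pregnant women follow hereafter the usual pregnancy programme and standard pregnancy regimen". An ultrasound follows at GA 37-38. No pedometer, week-form or other activity record is mentioned.

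Two further places matter. In the Standard regimen section, the dietician's first consultation includes an enquiry into activity habits, and all women are advised to be active. Under Project blood tests, the paragraph on the GA 37-38 ultrasound has the dietary history form completed a second time in all three groups.

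**The concern.** An effect of an intervention on activity is a comparison. It needs activity measured in the same way in the standard-regimen group or, less satisfactorily, a value in the pedometer groups from before they were told how far to walk. The text describes neither.

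Two things are at stake. First, one item of the leading purpose has no data to answer it, and a statistical analysis plan cannot recover values that were never collected. Second, the Hypothesis names physical activity as a means of limiting weight gain. If weight gain did not differ between groups, the trial would have limited means of telling whether activity failed to rise above that of the standard-regimen group or rose without affecting weight.

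**Working it through.** The plan gives no figure to reproduce here, so the check sets the measurements side by side.

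**1. Activity records described, by group and time.** Group size is 140 (420 / 3, as in the calculation of strength for part-project B).

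| | Group 1 | Group 2 | Standard regimen |
|---|---|---|---|
| Dietician's enquiry at first visit | yes, unquantified | yes, unquantified | yes, unquantified |
| Step count before the target | 0 | 0 | 0 |
| Registration weeks after the target, per woman | 7 | 7 | 0 |
| Planned week-forms | 140 × 7 = 980 | 140 × 7 = 980 | 140 × 0 = 0 |

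The pre-target row is zero because the pedometer is handed out after randomisation along with the encouragement to reach 11,000 steps. The first registration week starts from GA 14+0, after that encouragement. It is an early on-treatment value, not a baseline.

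**2. What the randomised step contrast identifies.** Let *m* be mean steps under standard regimen, *a* the effect of pedometer plus target, and *d* the further effect of dietician follow-up.

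- Standard regimen: *m* (not observed)
- Group 2: *m* + *a*
- Group 1: *m* + *a* + *d*
- Group 1 minus group 2: *d*

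The activity effect *a* cancels from the only contrast available. Groups 1 and 2 give *m* + *a* as a sum, and without *m* it cannot be split.

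**3. Whether *m* can be supplied from elsewhere.**

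- *Assume no change under standard regimen.* This is not safe, because the standard regimen itself includes advice to be active.
- *Use the earlier project's average.* The 150% statement implies 11,000 / 1.5 = about 7,333 steps/day. This is not a randomised comparator, and the protocol does not give the BMI of the women behind it.
- *Use change over the seven registration weeks.* This shows the course of steps after the target was set, mixed with the course of pregnancy. It is not a change from before the intervention.

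**4. Whether activity is an endpoint.** The protocol lists three primary and eight secondary endpoints. None is activity.

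**The case against.** The strongest reply is that the forms are not visible. The history form, the dietary history form and the 360-question instrument are in appendices or in another study, and any of them might ask about activity. The dietary history form is completed by all three groups at the start and again at GA 37-38, so an item on it would give both a baseline and a follow-up value. This stands. A reader might infer that standard-regimen women have no activity value of any kind. The documents support that only for step counts and for what the protocol text describes. The overview table's silence on activity adds little, since it omits the pedometer weeks too.

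It can also be said that activity is not an endpoint, that the purpose is only to illustrate, and that steps fit the compliance purpose. The first part stands: a reader might infer that the main comparisons are compromised, and they are not. The rest stands in part. Compliance has its own bullet, whereas the first bullet speaks of an effect.

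Two more readings go too far:

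- *That the trial will judge its step counts against the earlier project.* The protocol uses that average only to explain the target and plans no such comparison. Nor does it establish that those women were a different population.
- *That a null weight result could not be interpreted at all.* Up to seven registration weeks per woman show whether the target was approached. Steps far below 11,000 would point to non-adherence, and steps near it would weaken that explanation. What is missing is the difference from standard regimen.

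**Conclusion.** The point holds for the measurements the protocol describes. Step counts are planned in two of three randomised groups, never before the target, and for none of the roughly 140 standard-regimen women. The effect on activity against standard regimen or baseline is therefore not estimable, and the group 1 versus group 2 contrast shows only the addition of dietician follow-up.

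This rests on two assumptions: that the dietician's first-visit enquiry yields no quantified value, since none is described, and that the unseen forms contain no activity item common to all groups. If such an item exists at both times, the gap reduces to naming it as the activity measure.

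The consequence is confined to one stated purpose and to the interpretation of a null weight result. It should be corrected, but it does not threaten the trial's endpoint analyses.

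**What to change.** Put the same few activity questions to all three groups at inclusion and at GA 37-38. The dietary history form is the natural place, because it is taken before the telephone randomisation and repeated at the later visit. The inclusion answers must be recorded before allocation is known. If a form already holds a suitable item, name it as the activity measure instead.

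Base the between-group activity effect on that item: the GA 37-38 value compared across groups, adjusted for the inclusion value. Treat step counts as adherence data, summarised in groups 1 and 2.

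The cost is a few questions on forms already in use. Self-report is less precise than steps, and women who know their step target may report more activity, so the result should be read with that in mind.

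If no common item is used, reword the purpose so that, for activity, it covers only the description of step-count adherence in the pedometer groups. That costs a wording change, and the effect on activity is then no longer claimed.

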**PURPOSE:**

- To analyse the importance of changes in elements of the diet for maternal weight gain, length of pregnancy and complications of pregnancy.

**MATERIALS AND METHODS**.

1. **Randomised intervention study. Effect of physical activity measure with use of a pedometer together with dietary intervention in heavily obese pregnant women.**

Hypothesis:

Physical activity and or intensive dietary intervention will lessen material weigh gain during pregnancy in obese pregnant women and lessen the risk of

1. pathologic glucose tolerance during pregnancy and thereby the risk of GDM.

2. macrosomia.

3. reduce risk of caesarean section because of dystocia.

**Inclusion criteria:** BMI ≥30 kg/m².

Normal pregnancy with normal neck fold scan. Informed consent.

**Exclusion criteria:** Under 18 years. Non-Danish speaker. Serious disease in mother or fetus. Alcohol or drug dependency.

**Inclusion period**: 18 months during which 600 children are born at Hvidovre Hospital of mothers with a pre-pregnancy BMI ≥ 30 kg/m². With an expected participation percentage of 70, we expect to include 420 in the study.

In accordance with the standard regimen, all obese pregnancy women with BMI≥30 are offered:

**Standard regimen:**

- Clinical dietician: a general consultation with dietary advice and a detailed dietary history. (see below)
- Recommendation regarding physical activity, for instance rapid walking 30 minutes/day.
- Offered consultation with anaesthesiologist regarding course of birth, epidural, etc.
- Screening for GDM with OGTT in weeks 13-20 and 27-30
- In addition to neck fold scan in GA 11-13 and deformity scanning at GA 18-22 US (ultrasound) determination of fetal weight at GA 37-38
- Delivery according to departmental instructions.

Content of initial advice by dietician:

- Weight, detailed dietary history with completion of a diet form (see appendix 3), attempt to determine behavioural patterns in relation to diet and physical activity. The largest and most importance problems are dealt with in the initial phase.
- Individual dietary advice on hypocaloric, low fat diet of 5000–7000 kJ, corresponding to “Mediterranean diet”, based on the 8 dietary suggestions and a healthy and varied diet. Written information handed out.

**Overview of study d**esign:

|  | Dietary history | Blood tests | Other |
| --- | --- | --- | --- |
| Inclusion / randomisation | X |  |  |
| 13-20 |  | OGTT + project tests |  |
| 27-30 |  | OGTT + project tests |  |
| 37-38 | X |  | US |
| Birth |  |  | Cord Blood Tests |
| 8 weeks pp |  |  | Child’s height and weight  Breastfeeding |
| 1 year pp |  | OGTT + project tests | Childs height and weight |

**Method:**

After the first visit to the dietician during which a detailed dietary history is taken, all included obese pregnant women will be telephone randomised 1:1:1, to intervention groups 1, 2 or to general standard regimen for all obese pregnant women as given above.

**Intervention aim:** Weight gain: <5 kg

**Intervention group 1:**

- Receive follow-up dietary advice by alternatively personal or telephone contact every 2nd week. Given pedometer and advised to take 11,000 steps/day. This corresponds to 150 % of average for pregnant women, determined in previous project. Activity monitored for 7 consecutive days every 4th week.
- Follows in addition the normal pregnancy program and the other aspects of the standard regimen.

**Intervention group 2:**

- As intervention group 1, but without intensive follow-up by dietician.

**Inklusion and obtaining consent:**

All pregnant women with pre-pregnancy BMI ≥30 kg/m² will be summoned by letter to the dietician after receipt of notice of pregnancy by the visiting midwife at Hvidovre Hospital from the GP. To all pregnant women with BMI≥30 kg/m² who fulfil the inclusion criteria is sent:

- Written information on the project (appendix 4),
- The folder: “Your rights as a research subject in a biomedical project”
- History form (appendix 1a).

At time of visit the patient is offered:

- Consultation with dietician according to standard regimen. Dietary history form (appendix 1b) as used by all dieticians.
- Immediately hereafter, consultation with project leader with oral information on the project and receipt of informed consent (signing of consent form) in separate room. If the patient wishes to receive information on the project on another day, for instance, if they want someone to be with them, this is then arranged. If the patient wishes to have time to consider participation after being informed of the project, then a new meeting is planned with the project leader either the same day or another day.
- After the information consultation and written consent: Randomisation to intervention group 1, intervention group 2 or standard regimen (telephone randomisation).

Pregnant women with BMI≥30 kg/m² are then divided into the following 5 groups:

1. Intervention group 1: Pedometer + intensive dietary advice.
2. Intervention group 2: Pedometer.
3. Pregnant women who follow normal pregnancy program and standard regimen.
4. Pregnant women who come to a consultation with the dietician, but who **do not** wish to take part in the project.
5. Pregnant women who do not respond to summons to dietician and who have not received oral information about the project.

**Procedure for the 5 groups of pregnant women:**

1. Intervention group 1:
   - After the consultation with the dietician, the project leader assures that the history form is filled out and goes through it with the pregnant women.
   - Project leader informs about dietician follow-up program.
   - Project leader hands out pedometer and encourages a step count of 11,000 steps a day. Together with the pedometer is given: 7 copies of week-form for registration of step count (Appendix 2) and 7 return envelopes so that the week-forms can be returned on-going. Those included measure physical activity during 1 week every 4th week during the whole pregnancy. (circa GA 14,18, 22, 26, 30, 34, 38) On this form current weight is noted. The first pedometer week beginning as soon as possible from GA 14+0. SMS contact from project leader the day before the start of every registration week is offered. Written permission for this is obtained. (Appendix 6)
   - Maternal weight noted.
   - US planned by project leader at GA 37-38.
2. Intervention group 2:
   - After the consultation with the dietician, the project leader assures that the history form is filled out and goes through it with the pregnant women.
   - Project leader informs about dietician follow-up program.
   - Project leader hands out pedometer and encourages a step count of 11,000 steps a day. Together with the pedometer is given: 7 copies of week-form for registration of step count (Appendix 2) and 7 return envelopes so that the week-forms can be returned on-going. Those included measure physical activity during 1 week every 4th week during the whole pregnancy. (circa GA 14,18, 22, 26, 30, 34, 38) On this form current weight is noted. The first pedometer week beginning as soon as possible from GA 14+0. SMS contact from project leader the day before the start of every registration week is offered. Written permission for this is obtained. (Appendix 6)
   - Maternal weight noted.
   - US planned by project leader at GA 37-38.
3. Pregnant women who follow usual pregnancy programme and standard regimen.

- After consultation with dietician, the project leader assures that the history form is filled out and goes through it if necessary with the pregnant women.
- Then pregnant women follow hereafter the usual pregnancy programme and standard pregnancy regimen.
- US planed by project leader at GA 37-38.

1. Pregnant women who come to consultation with the dietician, but who **do not** want to take part in the project:

- After consultation with dietician the project leader requests that the history form is filled out and goes through it.
- The pregnant woman follows the usual pregnancy programme and standard regimen.

1. Pregnant women who do not respond to summons to the dietician and who have not received oral information about the project:

- The pregnant woman comes to a consultation with a doctor in accordance with the standard regimen in order to arrange a malformation scan at GA 18-22. The history form is asked about. If this has not been filled out, it is given out again and the pregnant woman is asked to fill it out.

**Project blood tests:** In all three groups an oral glucose tolerance test (OGTT) is done as part of the standard regimen at 13–20 and 27–30 weeks. In connection with these tests, blood will be taken for determination of c-peptid, CRP and lipid profile, (triglycerides, HDL, LDL, and total cholesterol) A research biobank will be set up (20 ml blood per blood sampling session) with the aim of later determination of, among others, IL-18, IL-6, TNF alfa.

Blood tests will be stored for 10 years

The material will only be used for analyses regarding determination of conditions related to pregnancy, physical activity, diet and obesity.

Plasma glucose and OGTT measured regularly at the department of biochemistry using routine methods.

For the OGTT the patient is fasting and ingests 75 g glucose. Plasma glucose determined initially and after 2 hours.

Extra tubes for measurement of markers for glucose metabolism are centrifuged, pipetted off and stored at –80 degrees until later analysis.

**Cord Blood samples** are taken immediately after birth and cutting of umbilical cord. If possible up to 20 ml blood is taken, and stored in the research biobank.

**Ultrasound (US) scans at GA 37-38:** Estimation of weight and measurement of amniotic fluid. This is done by project leader in patient groups 1, 2 and 3. In connection with this, the dietary history form is filled out again (see below) and the patient weighed.

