**Primary endpoints:**

Maternal weight increase

Birth weight – in relation to GA

Method of birth: uncomplicated vaginal birth / instrumental delivery / sectio

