**ETHICAL CONSIDERATIONS:**

There is no risk or side effects associated with participation in the project . It is expected that the women randomised to intervention will have a reduced risk of developing pregnancy and labour complications and that the results can be expected to be important for the future treatment of obese pregnant women.

Positive as well as the negative results will be published in a scientific medical journal.

The project will be reported to Datatilsynet (Danish Data Protection Agency) and the medical ethics committees.

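### The GA 37-38 fetal-weight scan is assigned to the project leader, who very probably knows each woman's arm, leaving an avoidable unmasked route to induction and method of birth

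*Protocol*

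**What the plan says.** **Arm-specific contact.** Under the Protocol's section on inclusion and consent, the project leader gives the oral information and receives consent; telephone randomisation follows. Under the procedure for the five groups, the tasks then differ by arm. In intervention groups 1 and 2, "Project leader hands out pedometer and encourages a step count of 11,000 steps a day", and "SMS contact from project leader the day before the start of every registration week is offered". Pedometer weeks run to about GA 38. In the standard-regimen group no pedometer is given, but the project leader still reviews the history form if necessary and arranges the late scan: "US planed by project leader at GA 37-38".

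**The scan.** The paragraph on ultrasound at GA 37-38 describes it as "Estimation of weight and measurement of amniotic fluid" and adds "This is done by project leader in patient groups 1, 2 and 3". The dietary form is completed again and the woman is weighed in connection with it.

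**Its place in care.** The standard regimen, offered to all obese pregnant women, lists the late fetal-weight scan. The next item says that delivery follows the department's instructions, whose content is not given.

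**Endpoints and expectation.** One of the three primary endpoints is "Method of birth: uncomplicated vaginal birth / instrumental delivery / sectio". Induction is a secondary endpoint. The hypotheses include less macrosomia and fewer caesareans for dystocia, and the ethics section states: "It is expected that the women randomised to intervention will have a reduced risk of developing pregnancy and labour complications".

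**The concern.** Women and dieticians cannot be masked to a pedometer and diet programme, but the person holding the ultrasound probe can be. The plan instead gives the scan to someone who delivers part of the intervention. Estimated fetal weight depends on the operator, and the protocol puts the expected direction in writing.

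If estimates came out somewhat lower in intervention women, or higher in controls, and if the estimate informs how birth is planned, induction and caesarean rates could differ between arms without any effect of diet or activity. Such a distortion would act on the care given, so a later analysis could detect signs of it but could not undo it.

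**Working it through.** The point rests on reading passages together; the protocol gives no figure for it. Each link is taken in turn.

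| Link | Status in the protocol |
| --- | --- |
| The project leader performs the scan in all three randomised groups | Stated |
| The project leader hands out pedometers and offers SMS contact in groups 1 and 2 only | Stated |
| The project leader knows the arm when scanning | Inferred: tasks differ by arm, and SMS contact, where accepted, can run to about GA 38. Who makes the randomisation call is not stated, and recall of every woman is not certain |
| The scanner is masked, or the result withheld | No such provision |
| The result is available before delivery | Inferred from the timing and from the scan's place in the standard regimen. Women who deliver before the scan are unaffected |
| The estimate influences induction or caesarean section | Possible; not stated |
| Method of birth is primary and induction secondary | Stated |

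**Illustration of what a shift would do.** Inputs:
- n = 140 per arm, the planned number including the dropout allowance, from the sample-size paragraph of part-project B.
- Two-sided 5% test of one pairwise contrast (assumed here).
- Control caesarean rate p1 of 20%, 25% or 30% (assumed; the protocol gives none).
- Shift d of 3 or 5 percentage points caused only by knowledge of the arm (assumed), so p2 = p1 − d.

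Formulas, by normal approximation:

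SE = √{[p1(1 − p1) + p2(1 − p2)] / n}

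Rejection rate = Φ(d/SE − 1.96) + Φ(−d/SE − 1.96)

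Worked case, p1 = 0.20 and p2 = 0.17: SE = √[(0.1600 + 0.1411)/140] = 0.0464; d/SE = 0.03/0.0464 = 0.647. The rate is Φ(−1.313) + Φ(−2.607) ≈ 0.095 + 0.005, which is 9.9% before rounding of the terms.

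| Assumed control rate | 3-point shift | 5-point shift |
| --- | --- | --- |
| 20% | 9.9% | 19.7% |
| 25% | 9.1% | 17.1% |
| 30% | 8.6% | 15.5% |

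In numbers of women, 0.03 × 140 = 4.2 and 0.05 × 140 = 7 per arm. The table shows what a shift of that size would do from any source. It does not show that this scan would produce one.

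**The case against.** **The central link is missing.** The protocol does not say whether the estimate enters the departmental instructions, at what threshold, or who decides. Fixed instructions would limit discretion. This stands, and it is why the point is worded as something that could happen.

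**Much of the endpoint is decided in labour.** Dystocia arises in labour, and instrumental delivery is decided there. Nothing shows that those decisions use the scan, and estimated fetal weight is not itself an endpoint. This stands too: the route is indirect and reaches only part of the primary endpoint.

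**The magnitude is assumed.** Correct. A reader might infer from the table that the trial's false-positive risk is two to four times nominal. The document does not support that, since both the caesarean rates and the shifts are assumptions.

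**One operator gives uniform measurement.** This is a real advantage, but extra scatter affects all arms alike, whereas an expectation effect would differ by arm.

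**Masking the scanner is only partial.** The women know their group, those deciding on delivery are not masked, and the project leader would still weigh the women although maternal weight gain is primary. (The clinical-data section takes the final weight from the pregnancy chart; whether that includes this weighing is not said.) All of this stands. It limits the gain but does not justify leaving open a route that is easily closed.

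**Conclusion.** The concern holds as a design weakness of minor priority. The protocol places the late scan, a routine-care measurement made before delivery, with a person who very probably knows the arm, and it provides no masking. Expectation could therefore reach induction and the caesarean component of method of birth.

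This rests on two inferences, that the arm is known at the scan and that the result is available before delivery, and on one unstated possibility, that the estimate affects delivery decisions. The size cannot be derived from the document.

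Two stronger readings are tempting. One is that the project leader certainly knows every woman's arm; the text makes this very likely but does not state it. The other is that method of birth will be biased; the text shows an open route, not a demonstrated effect. The passages do not contradict one another here, and no sample-size figure changes.

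**What to change.** In the procedure for the five groups and in the paragraph on ultrasound at GA 37-38, state that the scan in groups 1, 2 and 3 is done under the standard regimen by departmental scanning staff who are not told the group, and that women are asked not to disclose it. The dietary form and weighing can stay with the project leader.

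Add a check: compare estimated minus actual birth weight between arms, allowing for the interval from scan to birth. Birth weight is already a primary endpoint, so the only extra need is to record the estimate and the scan date. The check can reveal skewed estimates; it cannot reverse a delivery decision already taken.

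**Cost.** No visit or procedure is added, because the standard regimen already offers this scan to all obese pregnant women and the protocol reserves the project leader only for groups 1 to 3. The late appointment is shared between two people, and more operators may add some scatter, equally in all arms. The women and those deciding on delivery remain unmasked.

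Moving the pedometer and SMS tasks to the dietician is not a good alternative. Group 2 is defined by the absence of intensive dietician follow-up, so added dietician contact there would blur the comparison of group 1 with group 2.
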